### Outcome measures

The major outcome variable is HbA1c, measured at baseline and 3 and 6 months. HbA1C will be compared with the control (routine) group and with the other groups in this factorial design. This will also be compared within one group: baseline to 3 months and baseline to 6 months. We will explore between-group variation and within-group variation and any interactions between the groups over time.

In addition, secondary outcome variables will be number of all hypoglycemic episodes (blood glucose < 70 mg/dL (3.9 mmol/L) and ketoacidosis episodes (hyperglycemia blood glucose > 11 mmol/L, venous pH < 7.3, or serum bicarbonate < 15 mmol/L, ketonemia blood ß-hydroxybuyrate ≥ 3 mmol/L), taken as a composite variable at baseline and 3 and 6 months [30–32]. Total number of abnormal episodes counted over the follow-up period will be considered as a composite outcome.

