**Fig. 2 Fig2:**
[figure not shown]
Logbooks for groups A and C to record their daily blood sugar readings and insulin doses and for groups B and D to record daily blood sugar readings, insulin doses, and step count

**Table 1 Tab1:** Mobile messages by group

E-MESSEGES FOR GROUP C	E-MESSEGES FOR GROUP D
Remember to check your blood sugars before every meal and record it in your logbook. Keep up the good work.	How many steps have you taken today? Make sure your fitbit is charged to record all that hard work! Good luck and have a healthy day
Don’t forget to check and record your blood sugar and insulin dose in your logbook. This record will help you to discuss it with your doctor and make your sugar levels near to the targets. Have a good day!	Recording your step count can help you to manage your blood sugar, so Fitbit is here to help you to count your steps daily. Don’t forget to charge it. Have a good day!
Keeping an eye on your blood sugar. Knowing this can help you and your doctor to adjust your food choices and insulin doses accordingly. Thanks for checking and recording it in your log book!	Remember! Any type of physical activity you do will help you lower your blood glucose! It’s time to go for a walk and increase your daily steps. Fitbit is here to count your every step so don’t forget to note your steps daily in your logbook. Thank you for all your hard work!
Self-testing of your blood sugar is an important tool in managing your treatment plan and preventing diabetes complications, so try to keep your blood sugar levels record in your logbook as suggested by your physician and help yourself and your doctor to manage your treatment accordingly.	Fitbit is with you to count your steps during housework, outdoor work, job activities, recreational activities, and exercise. So charge you fitbit as required and don’t forget to record your steps daily in logbook. Thanks
Self-monitoring of blood sugar levels provides useful information for diabetes management as it can help you reach your overall treatment goals. So keep checking and recording it in your logbook. Good day!	Improved fitness lowers your blood glucose level, relieves stress, helps insulin work better and strengthens the heart, muscles, and bones. It’s time to set your goals and make your life healthier. Wear your fitbit device all the day and record your steps in log book. Don’t forget to charge it. Stay Healthy!

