### Data collection tools

At baseline we will determine the socio-demographic profile of patients, along with user satisfaction of maintaining log books and using the e-device for measuring step count. Additionally, clinical information for T1D and other co-morbidities, including age of onset, duration, complications, hospitalizations, habits for managing T1D, and other lifestyle characteristics, will be ascertained.

Two other tools will supplement data collection at baseline (0 months) and 3- and 6-month visits; namely, a 24-hour dietary recall [33] and physical activity assessment using both the International Physical Activity Questionnaire (IPAQ) and Youth Physical Activity Questionnaire (YPAQ) [34] (Table 2). The designed questionnaires and tools will be modified for clarity and cultural relevance after pilot testing on at least five T1D patients prior to initiation of the study. All groups will be followed up overall for a total period of 6 months. During these 6 months data for any additional clinic/hospital visit will be obtained from the medical record files of participants.

**Table 2 Tab2:** Assessments that will be carried out in the study and data collection time points (baseline, 3 months, and 6 months)

Variable	Component	Measurement tools/questions	Baseline	3 month	6 month
Socio-demographic measures		Age, Sex, Weight, Height, Marital Status, Education, Occupation and Parents Education, Occupation and Family history of diabetes	✓		
Health Related Information		History of Diabetes and History if comorbidities	✓		
		Episodes of complications, any hospital admission, Frequency of self-monitoring of blood glucose, frequency of maintaining log book	✓	✓	✓
Behavioral Measure		Frequency of visit to diabetic clinic, frequency of visit to dietitian	✓	✓	✓
	Daily Physical activity of 1 week	Questionnaire adapted from IPAQ and YPAQ	✓	✓	✓
	Barriers to physical activity	Questionnaire adapted from IPAQ and YPAQ	✓	✓	✓
	Dietary Intake	Self-Reported 24- Hour Dietary Recall Questionnaire	✓	✓	✓
Biochemical measures	Pathology	HbA1C	✓	✓	✓

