### Data analysis

We will use an intention-to-treat (ITT) analysis to evaluate changes in HbA1C and abnormal episodes of hypoglycemia and ketoacidosis. Generalized estimating equations will be used, with HbA1C readings at different points in time as our outcome variable. The mean change in HbA1C due to interventions will be estimated at 3 and 6 months, controlling for socio-demographic, clinical, nutritional, and physical activity variables. Secondary outcome variables are reported episodes of acute complications like hypoglycemia and diabetic ketoacidosis and will be recorded from interview-based data conducted at baseline and 3 and 6 months. In addition, these episodes will be further counted for the follow-up period using the daily log book of each participant.

Negative binomial regression will be used to observe the relationship among the four groups and number of episodes, adjusting for any socio-demographic, clinical, nutrition, and physical activity-related variables. If there is an excess number of ‘zeros’—meaning no abnormal episodes—then zero inflated negative binomial regression will be used instead of ordinary negative binomial regression. Twenty-four-hour dietary recall will be converted into total number of calories and percentage carbohydrate intake. Nutrition will be explored for total calories and food groups using factor analysis. Physical activity will be measured using step count data logged on a daily basis. These step counts will be used as time-dependent covariates for the final model. Step counts logged on a daily basis in two groups over a period of 6 months will be obtained from log books. The distribution of these data will be checked and, if needed, will be transformed. Changes in dietary habits and in step count over time will be used as a covariate in the final model. Physical activities reported during the three interviews will be converted into hours per week and categorized by type of activity as mild, moderate, and severe exercise.

In addition, we will explore blood glucose variability on a daily basis to calculate the average daily risk range for hypoglycemia using the standard method developed by Kovatchev and modified for relevant use by other investigators [15, 16].

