## Discussion

This randomized controlled trial tests the hypothesis that log book maintenance for SMBG will substantially increase among individuals receiving e-message reminders and will provide evidence for significant correlation between daily step count and blood glucose levels and overall changes in HbA1c in T1D patients. We further expect an interactive effect of e-message reminders and daily step count on blood glucose levels. Such interventions are necessary to bring about positive life style changes among T1D patients. Non-pharmacological interventions like these are user friendly, engaging patients with their home-based care and integrating them with health-care services. A multipronged approach is required to manage diabetes and reduce the severity of complications and our simple interventions include food diaries and physical activity logs together with managing blood sugar by insulin therapy [12, 13, 17, 20, 28].

There is reported evidence of a positive association of e-device with lifestyle changes and diabetes. Most lifestyle intervention studies using an e-device have been focused mainly on education related to advice on diet and physical activity for T2DM, but very few studies have focused on T1D and our study may add further evidence with regard to it [22–27]. Dissemination of this study will provide a potential tool in the form of a log book to be used by practicing physicians in low-resource settings. Additionally, the evidence generated from this study will be shared at various fora to help physicians or providers choose the most suitable lifestyle program for their T1D patients.

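### The acute-complication count adds log-book hypoglycaemia to ketoacidosis, so it can rise in message arms merely because more readings are logged, and the log book cannot identify ketoacidosis

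*Protocol article*

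**What the plan says.** Outcome measures (protocol article) sets the secondary outcome as the "number of all hypoglycemic episodes (blood glucose < 70 mg/dL (3.9 mmol/L) and ketoacidosis episodes", the latter defined by hyperglycaemia, "venous pH < 7.3, or serum bicarbonate < 15 mmol/L" and blood ketones. The two are combined: "Total number of abnormal episodes counted over the follow-up period will be considered as a composite outcome".

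Data analysis names two sources. Episodes "will be recorded from interview-based data conducted at baseline and 3 and 6 months", and in addition "these episodes will be further counted for the follow-up period using the daily log book of each participant". The number of episodes is compared among the four groups by negative binomial regression, or its zero-inflated form. Adjustment is for socio-demographic, clinical, nutrition and physical-activity variables. Neither the number of glucose readings nor the number of logged days is named as exposure.

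The Fig. 2 caption gives the content of the log book: "Logbooks for groups A and C to record their daily blood sugar readings and insulin doses", with step count added for groups B and D. Under Data collection tools, "data for any additional clinic/hospital visit will be obtained from the medical record files of participants". Table 2 there collects testing frequency and logging frequency at every visit, and HbA1c is its only biochemical measure.

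The group C messages in Table 1 ask patients to test before meals and write the result down. The Discussion states the hypothesis that "log book maintenance for SMBG will substantially increase among individuals receiving e-message reminders".

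**The concern.** A low glucose value reaches the log book only if the patient tests and records it. The messages are designed to increase exactly those two acts. If they work as intended, the arms differ in how completely hypoglycaemia is observed, and a comparison of raw counts mixes that difference with any real change in risk. The distortion is unfavourable to the messages: better recording looks like more complications and can hide a true reduction, which the Background and Rationale hope to show.

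Ketoacidosis has a different problem. Data analysis applies the log-book count to both kinds of episode, but a book of glucose values and insulin doses does not contain the pH, bicarbonate or ketone values that define ketoacidosis in Outcome measures. Those two sections and the Fig. 2 caption do not fit together. Adding a probably uncommon event to a count of low readings also leaves a total that says almost nothing about the uncommon one.

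This total is the outcome behind the secondary objective on acute complications.

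**Working it through.** The plan states no event rate, power or sample size for this outcome, so there is no figure to reproduce. The check has a textual part and an illustration.

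**Text**

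| Step | Place in the protocol article | Content |
|---|---|---|
| Definition | Outcome measures | glucose below 70 mg/dL, plus ketoacidosis, as one total |
| Source | Data analysis | interviews, and in addition the daily log book |
| Log-book content | Fig. 2 caption | glucose and insulin (steps in B and D) |
| Intervention target | Table 1, Discussion | testing and recording, expected to increase |
| Model | Data analysis | negative binomial on number of episodes, no exposure term named |

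**Effect of logging alone**

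Expected recorded hypoglycaemia = logged readings × P(reading below 70). With the same P in both arms, the rate ratio equals the ratio of logged readings. Assume 5% of readings are low over 182 days:
- 2 readings a day: 182 × 2 × 0.05 = 18.2 episodes
- 3 readings a day: 27.3, ratio 1.5
- 4 readings a day: 36.4, ratio 2.0

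A real benefit is cancelled when true ratio × logging ratio = 1. A logging ratio of 1.25 hides a 20% reduction (0.80 × 1.25 = 1.00), and a ratio of 2.0 hides a 50% reduction (0.50 × 2.0 = 1.00).

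**False-positive rate, 30 v 30**

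The arm size of 30 is from Sample size and sampling technique. Assumed: control mean m = 12, dispersion k = 1, no true effect, equal chance of a low value at every reading. For logging ratio r:

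SE = √[(1/m + k)/30 + (1/(m·r) + k)/30], z = ln(r)/SE, P(false excess) = P(Z > 1.96 − z)

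| r | ln r | SE | z | Closed form | Including simulations of the same test |
|---|---|---|---|---|---|
| 1.25 | 0.223 | 0.268 | 0.83 | 13% | 13–16% |
| 1.5 | 0.405 | 0.267 | 1.52 | 33% | 33–35% |
| 2.0 | 0.693 | 0.266 | 2.60 | 74% | 74–76% |

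That is roughly 15%, 35% and 75%, where 2.5% is nominal in that direction.

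**With an offset**

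Using log(logged readings) as offset, a simulation at 60 v 60 (mean 18.2, dispersion 0.5 to 1.0) brought two-sided rejection back to 4.7–5.9% at every logging ratio. This holds only if extra readings are as likely to be low as the others.

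**Share of ketoacidosis in the sum**

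Assume 0.05 to 0.3 ketoacidosis episodes per patient in 6 months, against 12 hypoglycaemia readings. The share is 0.05/12.05 = 0.4% to 0.3/12.3 = 2.4%. Halving the larger rate moves the total from 12.3 to 12.15, a change of 1.2%.

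**The case against.** **The log book is not the only source.** Interviews record episodes and hospital admissions at each visit, and medical records cover additional clinic or hospital visits, so ketoacidosis can be captured. This stands. What remains is that Data analysis also assigns ketoacidosis to the log book, and the article does not say which source decides. Interview reports of hypoglycaemia depend less directly on logging, but still need a low value to have been measured or noticed.

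**An exposure term is a detail for the analysis plan.** Partly fair: its absence alone would be no finding. But the article itself fixes the summed total, the log-book source, the model and the classes of covariate, and these choices together create the problem.

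**An offset can bias the other way.** This stands. Suppose 2 readings a day at 5% low, plus one prompted reading at 2% low. The count ratio is 0.12/0.10 = 1.2, while the rate per reading is 0.04/0.05 = 0.8, an apparent 20% benefit. The number of readings is also affected by the intervention. The offset therefore cannot be the only analysis.

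**The size is assumed.** This stands for every percentage above.

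Some stronger readings are tempting but not supported:
- A reader might infer that missing log books count as no episodes. No such rule is stated, and Data management says participants will be contacted about missing information.
- A reader might infer that episodes are counted twice. Nothing says that interview and log-book counts are added; they may be two measures.
- A reader might pool C and D for a 60 v 60 contrast with higher false-positive rates. Randomization and Interventions do give D log-book reminders, but the D messages in Table 1 concern steps and the device, and the stated model compares four groups.
- A reader might extend the argument to the average daily risk range. The article gives no formula for it, so no size can be derived here.

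**Conclusion.** The point holds as a should-fix on a secondary outcome. As written, the plan counts log-book hypoglycaemia in a way that depends on testing and recording, which the messages aim to raise, and it assigns ketoacidosis to a source that cannot identify it. The direction under equal risk per reading is clear: message arms, C against A above all, look worse. The size cannot be found from the documents. The rates of roughly 15%, 35% and 75% rest on the assumed mean, dispersion and logging ratios, and on prompted readings being as likely to be low as others. If prompted readings are less often low, the inflation is smaller. That ketoacidosis would be swamped also rests on assumed rates. The primary outcome, laboratory HbA1c, is untouched, so nothing here supports a claim that the trial's main conclusion is at risk.

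**What to change.** 1. Analyse hypoglycaemia and ketoacidosis as separate outcomes and drop the summed count.
2. Take ketoacidosis only from the interviews and medical record files already being collected.
3. Analyse log-book hypoglycaemia as a rate per logged reading (negative binomial with offset log of logged readings), and report readings per day by group.
4. Show interview-reported episodes as a separate analysis, not added to the log-book count.
5. Present the unadjusted log-book count beside the rate as a sensitivity analysis, and state in advance that a difference in log-book counts alone will not be read as harm or benefit.

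The cost is small. The data are already planned for collection and only analysis wording changes. The price is two secondary results instead of one, plus the sensitivity analysis.

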### Data collection tools

At baseline we will determine the socio-demographic profile of patients, along with user satisfaction of maintaining log books and using the e-device for measuring step count. Additionally, clinical information for T1D and other co-morbidities, including age of onset, duration, complications, hospitalizations, habits for managing T1D, and other lifestyle characteristics, will be ascertained.

Two other tools will supplement data collection at baseline (0 months) and 3- and 6-month visits; namely, a 24-hour dietary recall [33] and physical activity assessment using both the International Physical Activity Questionnaire (IPAQ) and Youth Physical Activity Questionnaire (YPAQ) [34] (Table 2). The designed questionnaires and tools will be modified for clarity and cultural relevance after pilot testing on at least five T1D patients prior to initiation of the study. All groups will be followed up overall for a total period of 6 months. During these 6 months data for any additional clinic/hospital visit will be obtained from the medical record files of participants.

**Table 2 Tab2:** Assessments that will be carried out in the study and data collection time points (baseline, 3 months, and 6 months)

Variable	Component	Measurement tools/questions	Baseline	3 month	6 month
Socio-demographic measures		Age, Sex, Weight, Height, Marital Status, Education, Occupation and Parents Education, Occupation and Family history of diabetes	✓		
Health Related Information		History of Diabetes and History if comorbidities	✓		
		Episodes of complications, any hospital admission, Frequency of self-monitoring of blood glucose, frequency of maintaining log book	✓	✓	✓
Behavioral Measure		Frequency of visit to diabetic clinic, frequency of visit to dietitian	✓	✓	✓
	Daily Physical activity of 1 week	Questionnaire adapted from IPAQ and YPAQ	✓	✓	✓
	Barriers to physical activity	Questionnaire adapted from IPAQ and YPAQ	✓	✓	✓
	Dietary Intake	Self-Reported 24- Hour Dietary Recall Questionnaire	✓	✓	✓
Biochemical measures	Pathology	HbA1C	✓	✓	✓

### Ethical considerations

Study participants will be asked to provide informed, written assent/consent prior to participation in this study. Appropriate assent/consent will be obtained by trained data collectors during face to face interviews; the data collectors will also make contact via phone call. Confidentiality of participants will be maintained throughout the follow-up. Study participants will be interviewed in areas separate to the clinical examination room and identification codes will be used to manage the data. This study will not impose any risk or discomfort on any patient or their parents, except for requiring their valuable time; however, this study intends to introduce beneficial lifestyle changes for improving the management of T1D by young adolescents and adults. Ethics approval from Aga Khan University Ethical Review Committee (AKU-ERC) was provided prior to initiating this study.

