It is time to check your blood sugar levels and don’t forget to keep recording of your sugar levels and insulin dose in you logbook. Thanks for your all efforts.	If you sit for long hours at work or at home, try to get up once every hour and take a quick walk around the room. Walking is a great way to get fit! So use your fitbit and record all the steps you have taken in the log book. Thanks you for your Hard work!

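### The no-risk statement conflicts with group D's activity messages, and the pooled, activity-adjusted episode count would show almost nothing of a change in ketoacidosis

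*Protocol article*

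**What the plan says.** Ethical considerations gives the risk statement without qualification: "This study will not impose any risk or discomfort on any patient or their parents, except for requiring their valuable time".

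The group D messages in Table 1 (Interventions) include "Any type of physical activity you do will help you lower your blood glucose", and the same message goes on to say that it is "time to go for a walk and increase your daily steps". A milder one suggests that people who sit for long hours "try to get up once every hour and take a quick walk around the room". All groups keep a log book of glucose readings and insulin. The Fig. 2 caption adds steps in two groups only, with log books "for groups B and D to record daily blood sugar readings, insulin doses, and step count".

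Outcome measures defines a hypoglycaemic episode as glucose below 70 mg/dL and defines ketoacidosis by glucose, venous pH or bicarbonate, and blood ketones. It then combines them: "Total number of abnormal episodes counted over the follow-up period will be considered as a composite outcome".

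Data analysis fits one negative binomial model (zero-inflated if needed) to the number of episodes, "adjusting for any socio-demographic, clinical, nutrition, and physical activity-related variables". It also says: "Changes in dietary habits and in step count over time will be used as a covariate in the final model". It does not say which model is meant by the final one.

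**The concern.** Three statements do not sit well together. The study promotes a behaviour because it lowers glucose, in patients who inject insulin and some of whom are under 18. It counts low glucose as a complication. And it says that taking part carries no risk.

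The episode outcome is where any such harm, or any benefit, would be seen. Its two components can move in opposite directions: more activity could raise hypoglycaemia, and better self-management could lower ketoacidosis. The Background and Rationale give ketoacidosis as a main reason for caring about acute complications, yet it is probably the rarer event and so the one that a single total shows least. If the model also adjusts for activity recorded after randomisation, it holds constant something that the messages are meant to change. The secondary objective of comparing acute complications across the groups would then be answered by a number that says little about ketoacidosis and may understate the effect of being sent the messages.

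**Working it through.** The protocol gives no episode rates, and its sample size rests on HbA1c, so there is no stated figure to reproduce. The first and last steps compare the text. The others use assumed values, shown as ranges.

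1. **Risk statement against intervention.** Ethical considerations excludes every risk except time. Table 1 promotes walking as glucose-lowering. Interventions has every patient log insulin therapy. Outcome measures counts glucose below 70 mg/dL. The first statement cannot stand beside the other three.

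2. **What the log book can detect.** It holds glucose, insulin and, in groups B and D, steps. It holds no pH, bicarbonate or ketones. A log-book count should therefore be mostly hypoglycaemia, and this is the reason for taking its share, s, as 90% to 99%.

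3. **Effect of pooling.** Let H and K be the true rate ratios for hypoglycaemia and ketoacidosis, and s the share of hypoglycaemia in the comparator arm. Then composite rate ratio = s × H + (1 − s) × K.

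| Scenario | s = 0.90 | s = 0.95 | s = 0.99 |
|---|---|---|---|
| H = 1.5, K = 1 | 1.45 | 1.475 | 1.495 |
| H = 1, K = 0.5 | 0.95 | 0.975 | 0.995 |
| H = 1.5, K = 0.5 | 1.40 | 1.45 | 1.49 |

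   For example, at s = 0.90 with H = 1 and K = 0.5: 0.90 × 1 + 0.10 × 0.5 = 0.95. A rise in hypoglycaemia passes through almost undiluted, and a halving of ketoacidosis nearly vanishes. Full cancellation in the third scenario needs s = 0.50: 0.75 + 0.25 = 1.00.

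4. **Same check from assumed rates.** With 0.2 ketoacidosis episodes per patient over 6 months and 2 to 50 hypoglycaemic episodes, ketoacidosis is 9.1% to 0.4% of the total. Halving it gives 0.955 to 0.998, and doubling it gives 1.09 to 1.004.

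5. **Precision of separate results, 30 v 30.** The 95% CI is the estimate divided and multiplied by exp(1.96 × SE).
   - Hypoglycaemia: SE = √((2a + 2/μ)/30), with assumed mean μ = 20 episodes per patient and dispersion a. For a = 0.5, SE = √(1.1/30) = 0.191, factor 1.46. For a = 1.5, SE = √(3.1/30) = 0.321, factor 1.88. Varying μ from 5 to 40 widens the range only to 1.44 to 1.93.
   - Ketoacidosis: SE = √(2/e), with e assumed episodes per arm. For e = 6, factor 3.10. For e = 3, factor 4.95. This allows for no overdispersion, so real intervals would be no narrower.

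6. **Adjustment.** Table 2 repeats the activity questionnaire at 3 and 6 months in all groups. If those values enter the episode model, the group D contrast is conditioned on something that the messages aim to change. Baseline activity would raise no such problem. If step count also enters that model, 60 of 120 patients (groups A and C) have no value, and a step-adjusted D v A or D v C contrast has no comparator data.

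**The case against.** The strongest reply is that the composite does not hide the harm at issue. Activity-related hypoglycaemia would dominate the total, and a 50% rise would appear as 1.45 to 1.495. That is correct. A reader might infer that no change in the composite could be attributed to either component, or that pooling conceals hypoglycaemia. The documents do not support this. Both event types are defined and recorded, so the limit lies in the outcome as stated and not in the data, and the loss falls mainly on ketoacidosis.

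A reader might also infer that group D is given no precautions against low glucose. That does not follow. The instruction sheet in the log book and the consent and assent forms are not shown, Table 1 need not be the full message set, and routine care continues in every group.

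It can further be said that component tables belong in an analysis plan, and that separate ketoacidosis results would be too imprecise to be of much use. The imprecision is real and limits those results to description. But the protocol does fix the outcome as a total and does name the adjustment, so this is more than missing detail. The planned average daily risk range for hypoglycaemia is a glucose variability score and does not replace an episode count.

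Finally, the step-count problem arises only if the unnamed final model includes the episode model. Activity from the questionnaires could be filled for all 120 patients. That objection stands, so the point is kept as conditional.

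**Conclusion.** The concern holds in a limited form. The no-risk sentence is wrong as written, because the activity messages carry a foreseeable risk of hypoglycaemia in insulin-treated patients. The protocol gives no figure for the size of that risk, and none is claimed here.

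The pooled count would register a rise in hypoglycaemia but barely register a change in ketoacidosis. This rests on hypoglycaemia making up 90% to 99% of episodes, which the log-book contents make plausible but the protocol does not state. Adjustment for physical activity could remove part of the messages' effect if the values used were measured after randomisation, which the text allows but does not specify. The sample size and the HbA1c analysis are not affected by this point. It is worth acting on because it bears directly on a stated secondary objective and is cheap to put right.

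**What to change.** 1. Replace the no-risk sentence with a statement that increased physical activity can cause hypoglycaemia in patients treated with insulin, and check that the consent and assent forms say the same.
2. Keep the composite, but also report hypoglycaemic and ketoacidosis episodes separately by arm. Give rate ratios with 95% CIs that are not adjusted for activity or step count during follow-up. Show self-monitoring frequency, already collected under Table 2, beside them, because a low reading is logged only if the patient tests and the reminders may increase testing. Label the table descriptive.

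The cost is one wording amendment and one extra table from data already being collected. At 30 per arm the intervals will be wide, especially for ketoacidosis, so the table can show direction but is unlikely to settle a difference.
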